## 8. STUDY INTERVENTION

### 8.1 Identity of Investigational Products (treatment)

Participants in the study will be given by their GP identically looking, numbered and marked medication glass jars with 5 daily doses of 40 mg (2 tablets of 20 mg per dose) of prednisone (intervention group) or placebo (control group). Oral and written instructions on how the medication should be taken will be provided to the study participants. The dosing schedule is very convenient for the participant as the medication needs to be taken only once a day during breakfast and for a clearly defined and limited timeframe of 5 days.

PREDNISON Galepharm Tabl. 20 mg will be delivered by Galepharm AG, [name]. For further information and details see product information of “PREDNISON Galepharm Tabl. 20 mg” (<https://compendium.ch/prod/prednison-galepharm-tabl-20-mg/de>). PREDNISON Galepharm as well as placebo tablets are manufactured according to Good Manufacturing Practice (GMP)-guidelines.

The University Hospital Pharmacy at the University Hospital Basel will procure the Prednison 20 mg Galepharm and the visually identical placebo tablets and the packaging material: medication glass jars and medication labels. The Pharmacy will be responsible for the manufacturing and the documentation of the investigational product and placebo used in this study.

#### 8.1.1 Experimental Intervention (treatment)

Patients in the intervention group will receive 2 white tablets of PREDNISON Galepharm Tabl 20 mg (oral corticosteroid) to be administered orally once daily for 5 days. One tablet contains the active substance Prednison (20 mg).

For further information and formulation details see product information for PREDNISON Galepharm Tabl. 20 mg, Swissmedic authorization 50821, Galepharm AG Zürich (<https://compendium.ch/prod/prednison-galepharm-tabl-20-mg/de>).

#### 8.1.2 Control Intervention (standard/routine/comparator treatment)

Patients in the control group will receive identically looking placebo (10 pills) manufactured by Apotheke Hotz, [name]. Each white tablet has a break mark, an average diameter of 9.00 mm, and an average height of 2.7 mm, identical to the verum tablets. Placebo tablets will be administered orally (40 mg of placebo once daily; 2 tablets of 20 mg) for 5 days. The content of the placebo tablets is as follows: Lactose monohydrate 140 mg, microcrystalline cellulose 68 mg, Croscarmellose sodium 5 mg, Magnesium stearate 2 mg.

#### 8.1.3 Packaging, Labelling and Supply (re-supply)

The University Hospital Basel Pharmacy will package and label the study medication with alphanumeric codes and dispense it according to the randomisation procedure i.e. 10 identically looking tablets of prednisone (intervention group) and placebo (control group). Tablets will be packaged in numbered and labelled medication glass jars with 5 daily doses of 40 mg (2 tablets of 20 mg) Prednison or placebo. The randomization list is provided by the Clinical Trial Unit Basel. Labeled glass jars containing 10 tablets each will be prepared as packages of 10 glass jars at the Hospital Pharmacy pick up by the study staff and delivered to every collaborating GP by study staff.

|                                                                                                                                           |                         |                 |
|-------------------------------------------------------------------------------------------------------------------------------------------|-------------------------|-----------------|
| [figure not shown] Universitätsspital
Basel
Spital-Pharmazie | Datum:                  | 07.11.19        |
|                                                                                                                                           | Seite:                  | 2 von 2         |
|                                                                                                                                           | Gültig ab:              | Siehe Deckblatt |
|                                                                                                                                           | Autorisierte Kopie Nr.: | Siehe Deckblatt |
|                                                                                                                                           | Dokumentnummer:         | SP1870-V01.docx |

  

|                                                                         |                      |
|-------------------------------------------------------------------------|----------------------|
| OSPIC Studie Placebo ODER Verum (Prednison)
20 mg) Tabletten 10 Stk. | Spezifikation |
|-------------------------------------------------------------------------|----------------------|

  

**5. Etikette(n):**  
[figure not shown]

Figure: Labelling sticker for the medication glass jars

#### 8.1.4 Storage Conditions

The medication must be stored in a dry place and at ambient temperature (15 – 25 °C). All medication (placebo and prednisone) is supplied, stored and eventually destroyed according to standard procedures at the University Hospital Basel Pharmacy (Please see Appendix Hospital Pharmacy Offer, 30Sep2019). The packed medication will be stored at the Pharmacy of University Hospital Basel at room-temperature up to the point of pick-up for distribution to GPs. The Hospital Pharmacy will continuously monitor room temperature and has a separate room with restricted access for all investigational medicinal products. The GPs and participant should store the glass jar in a dry place at room temperature.

## 8.2 Administration of experimental and control interventions

### 8.2.1 Experimental Intervention

Two tablets of PREDNISON Galepharm Tabl. 20 mg will be taken orally by the patient once daily during breakfast. The intervention group will receive prednisone for five days. Follow-up time will be 3 months from the start of treatment. In the event of a missed dose, patients are instructed to continue medication intake on the next day. Please see Appendix OSPIC Medication Guide\_V1.0.

### 8.2.2 Control Intervention

Two tablets of placebo will be taken orally by the patient once daily during breakfast. The control group will receive placebo for five days. Follow-up time will be 3 months from the start of treatment. In the event of a missed dose, patients are instructed to continue medication intake on the next day. Please see Appendix OSPIC Medication Guide\_V1.0.

## 8.3 Dose modifications

Due to the short intervention of 5 days, treatment modifications are not anticipated. However, treatment modifications are planned in the (unlikely) occasion of AE (e.g. allergic reactions to the study drug, psychotic, or pre-psychotic episode) or occurrence of SAE (e.g. sepsis, venous thromboembolism, fracture) (27) or other urgent reasons (pregnancy, cancer diagnosis, infection other than URTI). In any of those cases the treatment will be stopped immediately.

Treatment will also be discontinued when study participants withdraw their informed consent.

Treating doctors can change to open-label treatment and adjust treatment if they deem necessary for the benefit of the patients, such as in cases when the patients' clinical condition is worsening or the patient presents to the GP for consultation before the 5-day treatment is over. Throughout the trial, participants' treatment can be re-evaluated by their GPs based on clinical needs and GPs independently decide about additional treatment options. Please also see 7.4 Criteria for withdrawal/ discontinuation of participants.

## 8.4 Compliance with study intervention

Oral and written instructions on how the medication should be taken will be provided to the study participants. Participants are required to return empty medication glass jars to their GPs as soon as this is convenient for them (e.g. on the occasion of the next consultation). Participants will be asked by the research staff/ study nurse about their medication intake at the first phone call on day 7. In the event of a missed dose, patients are instructed to continue medication intake on the next day.

GPs will inform the patient in depth on the importance to adhere to the 5-day medication intake to ensure effectiveness of the treatment. The GPs will also remind patients on the importance for the trial conduct to be available for the follow-up phone calls. Furthermore, the dosing schedule is very convenient for the participant as the medication needs to be taken only once a day during breakfast and for a clearly defined and limited timeframe (5 days). Experienced and trained research staff/study nurses will call patients by phone on day 7, 14, 28 and at 3 months to complete the LCQ and to answer questions about other outcomes, in particular about medication intake (only on day 7), possible re-consultations with their GP, possible hospitalisation and the occurrence of AE or even SAE.

## 8.5 Data Collection and Follow-up for withdrawn participants

Participants in the study will be asked at each follow-up call at day 7, 14, 28 and after 3 months from enrolment whether they are still happy to participate in the study. Participants who wish to withdraw have the possibility to either (1) inform their GP who then records this in the participant file; (2) inform the study team directly by phone or mail; (3) inform the research staff at one of the follow-up phone calls. Participants who have withdrawn from the study will not be followed-up if they do not wish to be contacted. Data collected until the time of withdrawal will be used for the intention to treat analysis.

## 8.6 Trial specific preventive measures

Any co-treatment or co-medication (i.e. antitussives, inhalation, herbal teas, and homeopathic pharmaceuticals) is permitted except for the use of corticosteroids. The use of any other medical intervention by study participants will be recorded in electronic Case Report Forms (eCRF) to analyse potential influence on outcomes.

GPs will screen all female participants of reproductive age (postmenarche to menopause) using a battery of questions and will exclude all females who are pregnant, plan or are actively trying to get pregnant or women who are potentially pregnant. GPs will advise participants that they need to use contraceptives for the duration of the study and that they should inform the GP or the study team in case they suspect they have become pregnant. Women with anamnestic risk of a pregnancy shall be excluded from this study. If a participant gets pregnant during follow-up, course and outcome of the pregnancy should be followed up carefully by GPs, documented and reported. Please see section 10.1.2 for additional information on handling risk of pregnancy for this study.

## 8.7 Concomitant Interventions (treatments)

See section 8.6 ("Trial specific preventive measures").

## 8.8 Study Drug Accountability

The University Hospital Basel Pharmacy is responsible for all manufacturing and logistic documentation of the study medication up to the point of distribution to the GPs. Study medication packages will be stored in appropriate conditions at room temperature in a separate room dedicated to investigational medicinal products before being handed over to the study team which is responsible for delivering it to collaborating GPs. All participating GPs will receive a package with the required and pre-randomized medication necessary to recruit up to 10 participants. GPs will be in charge for the adequate storage of the study medication package and dispensing it according to protocol.

The Hospital Pharmacy documents in its accountability log the amount, the date and medication numbers of every manufactured medication batch and the picking up by study staff.

The GP documents the acknowledgement of receipt, the inventory at the site, the dispensing of the medication to the patient, and the return or alternative disposition of unused medication. The documentation should include dates, quantities, batch number, expiry date, and medication number, and this documentation should be available to the study monitor for review upon request.

## **8.9 Return or Destruction of Study Drug**

Return or destruction of left-over study medication are handled according to standard procedures and are the responsibility of the local study team.

Participants who complete the study are required to return empty medication glass jars to their GPs as soon as this convenient for them (e.g. on the occasion of the next consultation). Participants will be asked by the research staff/ study nurse about their medication intake at the first phone call on day 7.

In the case that the study medication intake must be stopped prematurely due to, for example, diagnosis of another serious illness or pregnancy, those participants will be asked to return the remaining study medication to their GP.

GPs who choose to stop collaboration in the study before reaching the recruitment target will have to return all study medication and documentation to the local study team in Liestal. In case that at the study end there is spare medication that was not used, those drugs will be returned to the local study team in Liestal who will be responsible to dispose of it.

Unused or expired medication may be returned by the local study team to the Hospital Pharmacy for destruction. In this case the destruction of the medication will be performed by an authorised company via high temperature incineration.

## 9. STUDY ASSESSMENTS

### 9.1 Study flow chart(s) / table of study procedures and assessments

#### Study Schedule

|                          | STUDY PERIOD          |                |                       |                                       |                    |                    |                      |
|--------------------------|-----------------------|----------------|-----------------------|---------------------------------------|--------------------|--------------------|----------------------|
|                          | Enrolment             | Randomisation  | Treatment             | Follow-up (T days/months ) |                    |                    |                      |
| TIME POINT               | T baseline | T 0 | T days 1-5 | T day7                     | T day14 | T day28 | T 3months |
| ENROLMENT         |                       |                |                       |                                       |                    |                    |                      |
| Eligibility              | X                     |                |                       |                                       |                    |                    |                      |
| Informed consent         | X                     |                |                       |                                       |                    |                    |                      |
| Allocation               |                       | X              |                       |                                       |                    |                    |                      |
| INTERVENTION      |                       |                | X                     |                                       |                    |                    |                      |
| ASSESSMENTS       |                       |                |                       |                                       |                    |                    |                      |
| Baseline characteristics |                       | X              |                       |                                       |                    |                    |                      |
| LCQ                      |                       | X              |                       | X                                     | X                  | X                  | X                    |
| Adherence to treatment   |                       |                |                       | X                                     |                    |                    |                      |
| Cessation of cough       |                       |                |                       | X                                     | X                  | X                  | X                    |
| Re-Consultations*        |                       |                |                       | X                                     | X                  | X                  | X                    |
| Hospitalisations         |                       |                |                       | X                                     | X                  | X                  | X                    |
| Concomitant treatments   |                       | X              |                       | X                                     | X                  | X                  | X                    |
| Adverse events           |                       |                |                       | X                                     | X                  | X                  | X                    |
| Serious adverse events   |                       |                |                       | X                                     | X                  | X                  | X                    |

\* Clinical follow-up visits with the GP are at the discretion of the treating GP and/or based on patient's needs

## Study Assessments Flowchart

[figure not shown]

## 9.2 Assessments of outcomes

On days 7, 14, and 28 and at 3 months patients will be called by a trained and experienced research staff/study nurse, and asked to complete the LCQ on the phone. Appointments for the next phone calls will be set during the previous phone call. At the follow-up phone calls the research staff/ study nurses will also inquire about the presence of cough (binary variable yes/no), adherence (day 7), number of re-consultations with the GP, hospitalisations for potential illness deterioration and the occurrence of AE and SAE events. Incidence rates of AE and SAE will be assessed in WHO-UMC (16) causality categories “certain”, “probable”, “possible”, and “unlikely” during 3 months following randomisation.

In case the phone is not answered, follow-up phone calls will be performed several times over the next days: at day 7 (+ 2 days), at day 14 (+2 days), and 28 (+2 days) and at 3 months (+7 days). Participants will also be sent reminder email provided the email was given by the participant. Data at follow-up will be recorded with eCRF. For each enrolled study participant, an eCRF is maintained. eCRFs must be kept current to reflect subject status at each phase during the course of study. Participants must not be identified in the eCRF by name or initials and birth date. Appropriate coded identification (patient ID) is used. GPs and the research staff/study nurses will be authorized to do paper and eCRF entries. Source data will be available at all GPs to document the existence of the patients. To ensure uniform questioning during the trial (LCQ) and to minimize differences GPs and research staff/study nurses will receive a trial specific training and standard operating procedure leaflet prior to study start.

### **9.2.1 Assessment of primary outcome**

At baseline GPs will hand participants the LCQ and will be available to answer question. Participants will complete the LCQ on paper. For the follow-up the LCQ will be administered by trained research staff and recorded electronically.

The LCQ total score (addition of domain scores) ranges from 3-21; a higher score corresponds to a better health status (30). Total and individual domain LCQ scores will be calculated. Please also see section 5.1.

### **9.2.2 Assessment of secondary outcomes**

A study research staff or research staff/study nurse will call participants at follow-up on day 7 (+ 2 days), day 14 (+2 days), and 28 (+2 days) and at 3 months (+7 days) to assess: 1) the impact of the treatment and placebo on patients' QoL at 7 and 28 days, as well as 3 months after randomisation, 2) cough-related QoL captured with the LCQ sub-domains physical, psychological, and social 7, 14, and 28 days, and 3 months after randomisation, 3) the overall cessation of cough 7, 14, and 28 days, and within 3 months after randomisation, 4) the incidence rate of re-consultations at GP and/or hospitalisations within 3 months following randomisation, 5) the total AE within 3 months after randomisation, 6) SAE within 3 months after randomisation. The secondary outcomes related to QoL will be measured as described for the primary endpoint. All other secondary outcomes will be measured using a study developed non-validated survey.

### **9.2.3 Assessment of other outcomes of interest**

No other outcomes are planned to be assessed.

### **9.2.4 Assessment of safety outcomes**

#### **9.2.4.1 Adverse events**

Corticosteroid potential side effects and complications are systematically recorded from the time of randomization (inform consent obtained at baseline) until the last follow-up calls at 3 months from randomization. Participants are informed and asked to immediately contact the GP or the study team in case of any possible side-effects. In case participants cannot reach the GP, they should visit the nearest hospital. This information is provided verbally and in writing to patients (Appendices Studieninformation\_OSPIC\_V1.0 and OSPIC Medication Guide\_V1.0). For safety reasons, the study team will also contact the corresponding GP to ensure patient follow-up is arranged as soon as possible. In case of persistent coughing at 3 months from randomization, the patient will be advised to visit the GP again for new assessment and necessary further investigations.

GPs and research staff/study nurses are instructed to document time of onset, duration, resolution, actions to be taken, assessment of intensity and relationship with study treatment. See section 10 (Safety) for AE definition and procedures.

#### **9.2.4.2 Laboratory parameters**

Not applicable.

#### **9.2.4.3 Vital signs**

At baseline (day 0, first presentation at GP) GPs will decide what diagnostics are necessary and, if applicable, will record for the purposes of the study the following: CRP test, white blood cell count, body temperature, blood pressure, pulse, O2 saturation, previous or present X-Ray, previous or present lung function assessment. After the inclusion in the study it is at the discretion of the treating GP to re-assess each participant at the general practice, when and as often as clinically needed regarding physical examination, lab testing, performing X-rays (e.g. chest), or decide to hospitalize the patient if indicated.

#### **9.2.5 Assessments in participants who prematurely stop the study**

GPs will inform the patient on the importance to adhere to the 5-day medication intake in a manner consistent with usual care recommendations to follow the treatment as prescribed. The GPs will remind participants on the importance for the trial conduct to be available for the follow-up phone calls. Participants are encouraged to answer the follow-up questions. If patients prematurely stop the study or do not answer the follow-up call, the study team can contact the GP to ask about possible GP visits (AEs or SAEs) or hospitalizations (i.e. for pneumonia). Data will be collected until the time of withdrawal and will be analysed in the intention to treat analysis.

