allergic reactions to the study drug, psychotic, or pre-psychotic episode, or Serious Adverse Events (SAE), sepsis, venous thromboembolism, fracture, can occur (27). In terms of side effects, a recently published retrospective cohort showed even a short time use of corticosteroids increases the incidence of severe adverse events such as sepsis or venous thromboembolism (28). Therefore, safety issues even with short time corticosteroids regimens are crucial. We feel that using the follow-up proposed for our trial will mitigate these concerns. A certain reassurance in terms of safety comes from the randomized-controlled trial conducted by Hay (17). In this study, assessing the effects of oral corticosteroids for acute lower respiratory tract infection in adults without asthma (prednisone 40mg once daily for 5 days, i.e. same dose as in our trial), no serious adverse events were observed (17). In any of the cases of adverse events occurring, as well as when other urgent reasons arise (pregnancy, new cancer diagnosis, infection other than URTI) (27), prednisone treatment will be stopped immediately. Other side-effects have been documented during short-term prednisone treatment: increase of appetite and activity, increased risk of infection, headache, glucose metabolism disorder (28). Study participants will be followed-up at several time points from enrolment in the study and experienced and trained study staff will call patients on day 7, 14, 28 and at 3 months and will ask participants to answer questions about outcomes and also the occurrence of AE or SAE. At the time of enrolment, participants will also be advised by their GP to contact the family practice or the study team in the event of any side-effects. We think that using the follow-up proposed for this study will mitigate the safety issues potentially posed even with short time corticosteroids.

Patients will not receive any financial compensation for study participation as the burden for them is minimal and they do not have any additional expenses for travelling, medical devices or other items.

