## **7.4 Criteria for withdrawal / discontinuation of participants**

Due to the short intervention of 5 days, no treatment modifications are planned unless in the (unlikely) occasion of AE (e.g. allergic reactions to the study drug, psychotic, or pre-psychotic episode) or occurrence

of SAE (e.g. sepsis, venous thromboembolism, and fracture) (27) or other urgent reasons (pregnancy, cancer diagnosis, infection other than URTI). In any of those cases the treatment will be stopped immediately. Treatment will also be discontinued when study participants withdraw their informed consent. Study participants are given the possibility to withdraw from the OSPIC trial without justification at every stage and at any time.

In the follow-up phone calls participants will be asked about concurrent medication, including if they started a treatment with antibiotics. In the case that participants are prescribed and start the antibiotics treatment during the study's 5-days medication, then those participants will be discontinued from the study.

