GPs will screen all female participants of reproductive age (postmenarche to menopause) using a battery of questions and will exclude all females who are pregnant, plan or are actively trying to get pregnant or women who are potentially pregnant. Women with anamnestic risk of pregnancy shall not be included in this study (unprotected sexual intercourse in the last two weeks). Pregnant participants must immediately be withdrawn from the clinical study. If a participant gets pregnant during follow-up, the course and the outcome of the pregnancy should be followed up carefully by GPs, documented and reported. Any pregnancy during the treatment phase of the study and within 30 days after discontinuation of study medication will be reported to [name]. med. [name] (Sponsor-Investigator) within 24 hours. The course and outcome of the pregnancy should be followed up carefully, and any abnormal outcome regarding the mother or the child should be documented and reported.

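### Minor: the protocol does not cleanly separate stopping treatment, or being taken out of the study, from refusing contact, so some day-14 LCQ scores could be forgone needlessly

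*Protocol*

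**What the plan says.** **Leavers.** Section 9.2.5 covers participants who stop early or do not answer a call. It encourages them to answer the follow-up questions and says that "the study team can contact the GP to ask about possible GP visits (AEs or SAEs) or hospitalizations". It ends with "Data will be collected until the time of withdrawal and will be analysed in the intention to treat analysis". Section 8.5, which is devoted to withdrawn participants, says "Participants who have withdrawn from the study will not be followed-up if they do not wish to be contacted". It adds that data gathered up to withdrawal enter the intention-to-treat analysis. It also sets when willingness is checked: "Participants in the study will be asked at each follow-up call at day 7, 14, 28 and after 3 months from enrolment".

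**Pregnancy.** Section 10.1.2 says "Pregnant participants must immediately be withdrawn from the clinical study". Elsewhere only the medication is stopped. Section 3.7 says that when "other urgent reasons arise (pregnancy, new cancer diagnosis, infection other than URTI) (27), prednisone treatment will be stopped immediately". Section 7.4 has "other urgent reasons (pregnancy, cancer diagnosis, infection other than URTI). In any of those cases the treatment will be stopped immediately", and 8.3 repeats it. Section 8.9 opens its instruction on returning tablets with "In the case that the study medication intake must be stopped prematurely due to, for example, diagnosis of another serious illness or pregnancy". Sections 8.6 and 10.1.2 both ask that the course of a pregnancy be followed.

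**Antibiotics.** Section 7.4 also discontinues from the study, not merely from treatment, anyone who starts antibiotics during the five days of study medication. Antibiotic use is asked about in the follow-up calls.

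**Use of the data.** The primary outcome is the LCQ score at day 14. It is analysed by intention to treat in all randomised patients (11.4.1, 11.4.2), with multiple imputation where data are judged missing at random (11.5).

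**The concern.** An intention-to-treat analysis needs outcomes from everyone randomised, including those who stop tablets or leave the treatment plan. Only a participant's refusal, or failure to reach them, should end collection. The protocol mixes three different events: stopping study medication, being taken out of the study by rule, and declining further contact.

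The timing makes this relevant. The first call is on day 7, one call before the primary outcome. A participant who says then that they no longer wish to take part, or who then reports antibiotics begun during the treatment days, would leave the study just before the day-14 LCQ. Under a literal reading of 9.2.5 that score is not collected and must be imputed, even if the person would have answered the phone.

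The antibiotic rule matters more than the pregnancy rule. Starting antibiotics is an event after randomisation that may reflect how the illness is going. Pregnancies in the relevant window should be close to none.

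A smaller issue is that GP contact after a stop is optional. Non-serious re-consultations in people who no longer take calls are then captured only if staff choose to ask.

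**Working it through.** **1. The exit rules side by side.**

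| Event | Section | What ends |
|---|---|---|
| Adverse event, cancer diagnosis, other infection | 3.7, 7.4, 8.3 | Study medication |
| Pregnancy | 3.7, 7.4, 8.3, 8.9 | Study medication |
| Pregnancy | 10.1.2 | Participation in the study |
| Antibiotics started in the five days | 7.4 | Participation in the study |
| Withdrawal, contact not wished | 8.5 | Follow-up |
| Withdrawal in general | 9.2.5, last sentence | Data collection, if read literally |

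Two rows remove a participant by rule, with no refusal involved. All four calls (days 7, 14, 28 and 3 months) fall after the planned last dose on day 5. Leaving the study therefore adds no protection from the drug beyond stopping the tablets. It can only cost outcome calls.

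**2. Calls at stake.** A person who exits at the day-7 call misses days 14, 28 and 3 months, which is 3 of 4 calls.

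**3. The plan's own sample size (11.2).** Inputs: difference 1.3, SD 3.3, two-sided alpha 5%, power 80%, 1:1 allocation. By the normal approximation,

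n per arm = 2 × (1.960 + 0.842)² × 3.3² / 1.3² = 101.2, rounded up to 102, so N = 204.

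This matches the protocol.

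**4. Largest number affected.** Sections 11.2 and 11.5 expect 10% and 5-10% drop-out.

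- 204 × 0.05 = 10.2 and 204 × 0.10 = 20.4, so about 10-20 patients, or about 5-10 per arm.
- At three lost calls each: 10.2 × 3 = 31 and 20.4 × 3 = 61, out of 204 × 4 = 816 planned calls.

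This is a ceiling. People who refuse or cannot be reached are missing under any wording, and the documents do not give their share. It also assumes that rule-based exits are counted within the 5-10%; no frequency of antibiotic use is stated.

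**5. Precision.** The half-width of the unadjusted 95% confidence interval is t(0.975, 2n−2) × 3.3 × √(2/n).

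| Analysed per arm | Half-width (LCQ points) |
|---|---|
| 102 (no loss) | 0.911 |
| 97 (about 5% loss) | 0.935 |
| 92 (about 10% loss) | 0.960 |

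Recovering every drop-out would narrow the interval by about 0.02 to 0.05 points, against an MCID of 1.3. Adjusting for baseline LCQ, as planned, would make these figures smaller.

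**6. What optional GP contact leaves open.** In-patient hospitalisation is a serious adverse event by definition (10.1.1). Section 10.1.3 commits to identifying and documenting all serious events and adverse events of interest, and GPs report adverse events to the study team (12.1). What remains is the count of non-serious re-consultations, otherwise collected in the phone calls (9.2).

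**The case against.** The strongest reply is that there is no true contradiction. Section 9.2.5 itself encourages participants to answer and allows GP contact after a stop, so its last sentence can be read, like its near twin in 8.5, as a rule for keeping data already obtained. Section 8.5 is the dedicated section and already leaves the door open to those willing to be contacted. After day 5 the calls are the only scheduled study activity, so someone who no longer wishes to take part is mostly declining the calls. Stopping tablets and leaving the study are compatible instructions for pregnancy, and 3.7, 7.4 and 8.3 largely repeat one list. Pregnancies should be very few after the screening in 7.1. Re-consultations are a descriptive count, and patients who miss one call are asked again at the next. Missing day-14 scores already have imputation and a complete-case sensitivity analysis.

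Most of this stands, and it limits the point to an ambiguity worth removing. It does not answer the rule-based exits. A participant discontinued for antibiotics, or withdrawn for pregnancy, has refused nothing. Section 8.5 speaks to the wishes of people who withdraw, and the protocol does not say that calls continue for those it removes.

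A reader might also infer that any early stop of tablets ends the calls. The documents do not say so: for adverse events, cancer or other infections only treatment stops. Nor do they support a claim that serious events go unrecorded, given 10.1.1, 10.1.3 and 12.1.

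**Conclusion.** The point holds as a minor, inexpensive improvement. Section 9.2.5 can be read as ending collection at withdrawal, and two rules (10.1.2 for pregnancy, 7.4 for antibiotics) move participants out of the study without their refusing contact. Together they could forgo a day-14 LCQ score that the primary analysis needs.

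The size is bounded by the planned drop-out: at most about 10-20 patients, and about 0.02-0.05 LCQ points of half-width even if all were recovered. This rests on SD 3.3, an unadjusted complete-case comparison, equal loss by arm, and rule-based exits lying within the stated 5-10%. The share that better wording would recover is unknown.

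A reader might infer that the intention-to-treat result is biased or that the trial is underpowered. The documents support neither. They give no frequency or arm difference for these exits, so no bias can be derived, and N, alpha and the power calculation stand.

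**What to change.** - **9.2.5, aligned with 8.5.** Replace the last sentence with, for example: *Data obtained before withdrawal are kept for the intention-to-treat analysis. For anyone who stops or is taken off treatment, LCQ calls (at least day 14) and safety follow-up continue unless the participant declines them.* Ask leavers once which items they still accept.
- **9.2.5, GP contact.** Turn the permission into a commitment: the team *will* contact the GP, where consent allows, and will ask about re-consultations as well as serious events and hospitalisations up to 3 months.
- **10.1.2 and the antibiotic rule in 7.4.** Replace withdrawal or discontinuation from the study with stopping study medication, while calls and safety follow-up continue unless declined.

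The cost is wording in four sections, one question to leavers, GP calls for at most about 10-20 patients (a contact 9.2.5 already permits), and possibly a line in the consent form, which is not among the documents. The right in 7.4 to leave at any time without giving a reason is unchanged.
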